### Randomization

After the baseline measurements, participants will be randomized by permuted block randomization based on computer-generated random numbers. The block size is fixed to contain 9 participants: 3 assigned to the control group, 3 to the HIIT group, and 3 to the AI-based coaching group. The participants are reinformed of the study design and procedures at the time of randomization. Study participants will be told that we study methods for reducing arterial stiffness during a 12-week intervention. The randomization procedure involves participants choosing 1 of 9 identically sealed opaque envelopes, which are in a mixed order containing the group assignment. The staff member who generates the random numbers and fills the sealed envelopes is independent of the individual who runs the randomization meeting, ensuring that the allocation sequence remains concealed until a participant chooses an envelope.

The complete randomization list will be stored electronically on a secure, access-restricted private server. Access is limited to the independent researcher and the designated data manager, and all access events will be automatically logged. For allocation or other study-specific purposes, separate working files containing only the minimum necessary information will be generated.

After randomization, study participants will be advised not to discuss issues related to group allocation during the assessments. All baseline data will be collected prior to randomization to prevent participants and study personnel from being biased due to group assignment. Outcome assessors will be blinded to the participants’ group assignment. The analysts conducting the primary analysis will be blinded to group codes until the ITT analysis is complete.

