## Methods

### Study Design

Guidance with Oura and AI for Reducing Arterial Stiffness (GONDOR-AS) is a 12-week randomized controlled trial (ClinicalTrials.gov identifier: NCT06644014) consisting of three groups (n=55 per group): (1) Oura Ring only (a control group), (2) Oura Ring+HIIT twice a week (*a physiological benchmark*), and (3) Oura Ring+AI-based coaching for steady-state aerobic training (no external supervision). A full structured abstract fulfilling World Health Organization Trial Registration Data Set version 1.3.1 criteria is provided in Checklist 1. This protocol adheres to the SPIRIT (Standard Protocol Items: Recommendations for Interventional Trials) 2013 Statement and SPIRIT-AI (Standard Protocol Items: Recommendations for Interventional Trials–Artificial Intelligence) extension guidelines (Checklist 2).

All groups will be blinded to their CVA/pulse wave velocity (PWV) information but will use identical Oura Ring devices. Apart from the AI-based coaching group, the Oura App experiences will also be identical. The primary comparison in this trial is explicitly between the AI coaching group and the Oura Ring only group. The supervised HIIT group is included as a “physiological ceiling” benchmark to show what is achievable under resource-intensive conditions.

The study will be implemented in collaboration with the Oura company and the Kuopio Research Institute of Exercise Medicine (KuLTu). Patients and the public were not involved in the initial design of this academic-industry collaboration protocol.

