#### AI-Based Coaching for Steady-State Aerobic Training

##### Overview

KuLTu serves as the onsite study center responsible for participant recruitment, baseline and follow-up measurements, supervised HIIT sessions, and the initial setup of study devices and applications. All subsequent participant interaction with the AI system occurs remotely through the mobile app.

The AI-based coaching condition will start immediately after the randomization when participants in this group will be given access to an additional AI coaching feature, unavailable to participants in the other study groups. The clinical trial will use the production version of the AI coach with the addition of a prompt to focus on encouraging moderate, steady-state exercises for 2 to 3 hours per week, also referred to as zone 2 cardio training.

The AI-based coaching feature and its supporting infrastructure are hosted offsite within Oura’s secure cloud environment. Physiological data captured by the Oura Ring are transferred automatically to Oura’s cloud servers via the participant’s smartphone, processed to generate individualized insights, and returned to the participant through the app interface. Oura maintains the offsite computational resources, data storage systems, and model update processes.

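### One published block size of 9, drawn from a pool of envelopes at a single centre, lets anyone who knows the earlier draws deduce some late allocations, so the concealment statement does not hold late in a block

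*Protocol article*

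**What the plan says.** All of the procedure is in the Randomization section of the protocol article. The method is permuted blocks: "participants will be randomized by permuted block randomization based on computer-generated random numbers". There is one block size, and it is printed: "The block size is fixed to contain 9 participants", made up of "3 assigned to the control group, 3 to the HIIT group, and 3 to the AI-based coaching group". Allocation is by physical draw: "The randomization procedure involves participants choosing 1 of 9 identically sealed opaque envelopes, which are in a mixed order containing the group assignment".

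The safeguard named is that the person who generates the numbers and fills the envelopes is not the person who runs the randomization meeting. The section describes this as "ensuring that the allocation sequence remains concealed until a participant chooses an envelope". It adds that "The complete randomization list will be stored electronically on a secure, access-restricted private server", with access limited to the independent researcher and the data manager. Outcome assessors are to be blinded, and baseline data are to be collected before the draw.

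Two other places matter. Under AI-Based Coaching for Steady-State Aerobic Training, Overview, the article says "KuLTu serves as the onsite study center responsible for participant recruitment, baseline and follow-up measurements, supervised HIIT sessions", so one centre does nearly everything in person. Under Study Measurements, Overview, baseline cfPWV and randomization fall at the same visit, about 2 weeks after the first visit.

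**The concern.** Opaque envelopes and independent filling hide what each envelope holds. They do not hide what has already been drawn. When the block size and its composition are both known, the contents of the remaining envelopes follow by subtraction. The arms are supervised cycling, an app coach and no added activity, so delivery staff will know who is in which arm once allocated. At a single centre, the person arranging or running the next randomization visit could plausibly know the earlier draws in the current block.

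What is at stake is selection at entry. Someone who can foresee the next arm could move a visit, encourage or discourage a participant, or take the baseline cfPWV measurement (a co-primary outcome) with an expectation in mind. Collecting baseline data before the draw does not help when the draw is already foreseeable, and blinded follow-up assessment does not undo selection at entry.

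**Working it through.** **Inputs.** Block of 9, three per arm (Randomization). Total 165 (Study Design; Recruitment of the Study Participants). The article gives no figure for predictability, so there is none to reproduce.

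**Assumptions.** (a) The nine envelopes are used up before a new set is laid out. (b) The observer knows the earlier draws in the block.

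**Which draws are certain.** With r envelopes left, the remaining set is a random r-subset of the nine. The next draw is certain when all r belong to one arm: P = 3 × C(3,r) / C(9,r).

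- Ninth draw (r = 1): 3 × 3 / 9 = 1.
- Eighth draw (r = 2): 3 × 3 / 36 = 9/36 = 0.25.
- Seventh draw (r = 3): 3 × 1 / 84 = 3/84 = 0.0357.
- Draws 1 to 6: never certain, since four or more envelopes cannot all belong to one arm.

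Sum per block: 1 + 0.25 + 0.0357 = 1.286 of 9, or 14.3%. As 165 = 18 × 9 + 3, there are 18 full blocks: 18 × 1.286 = 23.1, about 23 of 162. The last three participants would occupy positions 1 to 3 of a new block, where nothing is certain, so they add none.

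**How often a best guess is right.** The best guess is the arm with most envelopes left. Its success rate at each draw is the expected value of (largest remaining count)/r. Two worked cases:

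- Eighth draw: 0.25 × 1 + 0.75 × 0.5 = 0.625. At least one arm is always exhausted by then.
- Seventh draw: the three left split 3-0-0, 2-1-0 or 1-1-1 with probabilities 3/84, 54/84 and 27/84, giving 3/84 + (54/84)(2/3) + (27/84)(1/3) = 48/84 = 0.571.

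| Draw | 1 | 2 | 3 | 4 | 5 | 6 | 7 | 8 | 9 |
|---|---|---|---|---|---|---|---|---|---|
| Best guess right | 0.333 | 0.375 | 0.429 | 0.446 | 0.471 | 0.536 | 0.571 | 0.625 | 1 |
| Certain | 0 | 0 | 0 | 0 | 0 | 0 | 0.036 | 0.25 | 1 |

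The mean of the best-guess row is 0.532, against 0.333 by chance.

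**What varied block sizes would change.** This was simulated with 162 allocations and sizes equally likely. The guesser knows the menu of sizes and all earlier allocations, but not the size of the current block.

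| Block sizes | Certain | Best guess right |
|---|---|---|
| 9 only | 14.1% (exact 14.3%) | 53.3% (exact 53.2%) |
| 6, 9 | 5.1% | 54.3% |
| 6, 9, 12 | 2.5% | 53.0% |
| 3, 6, 9 | 3.8% | 55.3% |

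Varying the size removes most of the certainty but leaves best-guess success about where it was. Including blocks of 3 raises it.

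**The case against.** The strongest reply is that the deduction needs facts the article does not give. It does not say that the person running the meeting knows every earlier draw in the block. It separates that person from the one who fills the envelopes, and it restricts access to the list. It does not say whether participants draw singly or several at one meeting; if several drew together after completing baseline, there would be little chance to act on foresight. The opening is also narrow: participants have been screened, have done the ergospirometry test and have received the ring about 2 weeks earlier, and outcome assessors are blinded. All of this stands, and it limits the seriousness of the point. None of it restores the concealment statement, because no listed safeguard stops deduction from earlier draws.

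A reader might infer three stronger things that the article does not support.

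- **That free choice of envelope makes the stored list useless as a check.** The article does not say what the list records; it may include realised allocations. A blind pick among identical opaque envelopes is itself a random ordering and introduces no bias of its own.
- **That nine fresh envelopes are offered each time, so that this is really simple randomisation.** The stated method and the fixed block contents point the other way, and nothing in the text describes refilling.
- **That 55 per group is undermined because 165 is not a multiple of 9.** Fifty-five is a planning target. A departure of a participant or two per arm has a negligible effect on power.

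**Conclusion.** The concern holds in a limited form. With one disclosed block size of 9, the claim that allocation stays concealed until an envelope is chosen fails late in each block for anyone who knows the earlier draws: always at the ninth, in a quarter of blocks at the eighth, and rarely at the seventh. In total, 14.3% of allocations in full blocks are exposed to certain deduction.

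This rests on each set being used up before the next, which the permuted-block description implies, and on staff knowing the earlier allocations, which is plausible at one centre but not stated. The figures measure predictability. They are not an estimate of bias in cfPWV or VO2max, and nothing in the article shows that anyone acted on a deduced allocation. The point should be addressed, but it does not invalidate the trial.

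**What to change.** **Participants still to be randomised.** The same independent staff member prepares sequentially numbered sealed opaque envelopes, or sets up a central draw, to be opened strictly in the order of the stored list. Block sizes vary at random among larger sizes, for example 6, 9 and 12 but not 3, and are not disclosed to visit staff. Envelope number, date and time are logged at each opening.

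**Participants already randomised.** Correct the concealment statement, state whether each set of nine was used up before the next was laid out, and report baseline characteristics and allocation by position within block. A reader can then see whether late positions differ from early ones.

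**Cost.** A new list and a new set of envelopes, no extra staff, and possibly a slight imbalance in group sizes if the last block is incomplete. The benefit of the new procedure is confined to those not yet randomised. Recruitment began in October 2024, and data collection is due to end in March 2026 after a 12-week intervention (Results), so they may be few. The reporting part applies to everyone and costs little.

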### Interventions

#### Overview

Participants are instructed to maintain their usual diet, medication, and lifestyle (other than the assigned exercise or control condition) throughout the 12-week intervention. Starting new structured exercise programs or using other lifestyle-tracking devices is prohibited.

The control group will be instructed to maintain their physical activity unchanged during the study. Leisure-time physical activity at baseline as well as during the intervention period will be assessed by the Oura Ring in all 3 study groups.

The HIIT instructor will have the opportunity to motivate the participants in connection with the twice-weekly training sessions, which can be assumed to have improved adherence. The implementation of the AI coach was instructed in detail at the beginning of the intervention. Participants in all groups will be able to contact the research staff at any time if they wish.

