**Objective:**

We will study the comparative effectiveness of a wearable and an interactive app-based AI coaching intervention promoting moderate exercise in improving gold-standard cfPWV and VO_2_max. This will be compared to a supervised high-intensity interval training (HIIT) group (benchmark with known benefits for VO_2_max) and a control group using only the Oura Ring (passive monitoring). We will also conduct a detailed process evaluation (structured interviews) to study the feasibility and experience of interacting with the AI coach.

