**Methods:**

This randomized controlled trial will recruit 165 eligible sedentary participants aged 30 to 65 years. The co-primary outcomes, cfPWV and VO_2_max, are measured at baseline and will be repeated after 12 weeks. Participants are equally randomized into 3 groups: an AI-based coaching group (steady-state exercise), an HIIT group (supervised exercise), and a control group (usual low activity). The AI-based coaching group receives personalized guidance using large language model technology. All participants wear the Oura Ring and are blinded to the cardiovascular health metrics provided by the ring.

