In this trial, the AI-based coaching system functions as a consumer-facing digital health intervention aimed at supporting individuals in adopting and maintaining physical activity behaviors known to reduce arterial stiffness. AI-based coaching delivers personalized guidance, motivation, and feedback based on physiological and behavioral data collected by the Oura Ring, together with limited self-reported information. The AI system is intended for use by adults from the general population seeking to improve cardiovascular health outside formal health care settings. Within the trial, the AI system represents one of the behavior change strategies being compared to evaluate its efficacy in reducing arterial stiffness. The AI system does not inform clinical decision-making or patient management. Instead, the AI system provides automated, participant-facing support for lifestyle modification.

The purpose of this randomized controlled trial is to evaluate the effectiveness of an AI-based coaching intervention promoting moderate, steady-state exercise on improving both gold-standard cfPWV and VO_2_max. This takes place via a feedback loop where the user can freely interact with the AI and gain real-time insights drawn from their data. The study uses a 3-arm parallel design with 2 comparisons. The supervised high-intensity interval training (HIIT) group serves as the benchmark—a comparison whose well-documented advantage is a relatively rapid gain in VO_2_max. This group tests what is physiologically possible but might be challenging to adhere to long term, especially in the broad general population. The Oura Ring only group serves as the baseline comparator to isolate the effect of the AI-based coaching beyond the benefits of passive self-monitoring via the wearable. The primary outcomes are the changes in cfPWV and VO_2_max at 12 weeks. Process evaluation (interviews and chat logs) is conducted for understanding the qualitative aspects of feasibility and the mechanism of adherence for the novel AI coach.

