## Discussion

### Anticipated Findings

Study findings will determine what the effects of adopting a wearable device with built-in AI guidance and exercise on vascular aging or stiffness and cardiorespiratory fitness are. With any wearable technology, a critical objective is finding the “active ingredient”—is it simply the purchase of a new device and thus becoming more mindful of one’s behavior, or is it some specific feature of the device/app? To disentangle some of the correlated effects, we will use a control group that receives the ring itself with all the available data except CVA. Using this as a comparison, we can see if the added exercise makes a difference compared to just owning an Oura Ring. The supervised HIIT group is a well-known intervention that reliably improves VO_2_max. It is included as a “physiological ceiling” benchmark to show what is achievable under externally mandated, resource-intensive conditions, rather than as a direct variable-matched control. This comparison enables contextualization of the effectiveness of the AI-guided behavioral intervention in relation to established high-efficacy training paradigms.

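### The control arm is told to keep its activity unchanged, so the primary comparison does not isolate AI coaching beyond passive self-monitoring as the protocol says

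*Protocol article*

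**What the plan says.** Study Design fixes the primary comparison: "The primary comparison in this trial is explicitly between the AI coaching group and the Oura Ring only group". The Frequentist Analysis Plan repeats this and makes the other pairs exploratory.

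The document gives this comparison a purpose in three places:

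- The abstract's Objective labels the control arm as passive monitoring.
- The Introduction says the arm is there "to isolate the effect of the AI-based coaching beyond the benefits of passive self-monitoring via the wearable".
- Anticipated Findings asks whether the active ingredient is acquiring a device and becoming more mindful, or a particular feature of it. It answers that, with this control, "we can see if the added exercise makes a difference compared to just owning an Oura Ring".

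The conditions actually assigned are set out elsewhere. The Overview under Interventions says: "The control group will be instructed to maintain their physical activity unchanged during the study". The same section asks all participants to keep their usual lifestyle apart from the assigned condition, and adds: "Starting new structured exercise programs or using other lifestyle-tracking devices is prohibited". The abstract's Methods describes the control arm by its usual low activity. The AI arm uses the production coach with "a prompt to focus on encouraging moderate, steady-state exercises for 2 to 3 hours per week".

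**The concern.** A ring-only arm can show the benefit of passive self-monitoring only if its members are free to respond to what they see. For the two co-primary outcomes, the obvious response is to move more. An arm told not to change its activity is discouraged from that response, so the quantity that the Introduction says is being subtracted is not fully present in the control arm.

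At stake is the interpretation of the trial's primary result. A difference between arms could be reported as the coach's contribution over and above owning and watching the ring, when the design does not observe ring users left to themselves. The product is commercial and the plan includes dissemination through consumer channels, so the wording of this claim matters.

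**Working it through.** **1. The plan's own figure.** From Power Calculations: difference 0.4 m/s, SD 1.4 m/s, two-sided alpha .05, power 80%, pre-post correlation 0.86.

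- Unadjusted: n = 2 × (1.960 + 0.842)² × (1.4/0.4)² = 2 × 7.849 × 12.25 = 192.3, rounded up to 193 per group. This matches the plan.
- Covariance adjustment: 193 × (1 − 0.86²) = 193 × 0.2604 = 50.3, stated as 50.
- Attrition: 50 × 1.10 = 55.

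The calculation reproduces and is not in dispute. The 0.4 m/s comes from literature on aerobic exercise, with the pilot used to choose the conservative value. It is the size of an exercise effect. Nothing in that section derives it as an effect of coaching beyond self-monitoring.

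**2. What each arm receives.**

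| | AI arm | Control arm | Ring users left free |
|---|---|---|---|
| Ring and standard app | yes | yes | yes |
| AI coach with goal of 2 to 3 h/week | yes | no | no |
| Told to keep activity unchanged | no | yes | no |
| Present in the trial | yes | yes | **no** |

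The HIIT arm does not fill the last column. It has supervised training plus a home exercise target, and Anticipated Findings says it is not a matched control.

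**3. What the contrast estimates.** Let A be the mean change under AI coaching, C the mean change under ring plus instruction, and F the mean change that ring users without the instruction would show. The trial estimates A − C. The Introduction claims A − F. The two are linked by

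A − C = (A − F) + (F − C).

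The trial observes A and C but not F. The two quantities are equal only if F = C, that is, if the instruction makes no difference to the outcome. The document neither states nor supports that.

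**4. What can be said about F − C.** No figure in the document bears on it. It depends on whether self-monitoring alone would raise activity in these participants, by how much, and on how far controls follow the instruction. If self-monitoring does nothing, or if controls ignore the instruction, F − C could be near zero. The document does not fix its size or its sign.

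**5. Does another section resolve it?** Strengths and Limitations discusses language and theoretical grounding, not the control instruction. Results says that no separate analysis plan is currently planned. Anticipated Findings attributes the contrast to added exercise, which is closer to what is estimated, but sets it against merely owning the ring. That is again F and not C.

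**The case against.** Several counter-arguments have force.

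- **The instruction is mild.** Controls are asked to keep activity as it is, not to be inactive. Part of the restriction is common to the trial, since every participant is asked to keep usual habits outside the assigned condition. This stands, and the point should not be put as an order to stay inactive. The control arm nevertheless receives its own explicit instruction, which the AI arm does not.
- **The exercise goal is part of the coach.** Study Design names the arm as coaching for steady-state training, and goal setting is listed among the coach's techniques. A reader might infer that the goal confounds the comparison. The document does not support that: the goal belongs to the intervention as defined, and separating the two would need a further arm.
- **Both arms share the ring.** Devices are identical and the app differs only by the coach. The ring is issued about 2 weeks before randomisation, so early novelty is shared. This stands: ring wear and feedback unrelated to activity do cancel. What does not cancel is a later change in activity that controls are asked not to make.
- **The Discussion is hedged.** It claims to separate only some of the correlated effects and speaks of added exercise, and the statistical overview treats all conclusions as exploratory. This softens the Discussion but leaves the Introduction's claim to isolate the coach unchanged.

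A reader might also infer that the estimate is biased in favour of the AI arm by a definite amount, or that the trial is underpowered for the claimed effect. Neither follows. As an estimate of the contrast between the conditions assigned, the randomised comparison is sound, and any figure for the gap would rest on an invented self-monitoring benefit.

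**Conclusion.** The concern holds as a mismatch between a stated property of the primary comparison and the condition that the control arm is given. The comparison validly estimates the effect of AI coaching, including its exercise goal, against the same ring with an instruction to keep activity unchanged. It does not estimate the coach's effect beyond free self-monitoring, and it does not compare with simply owning the ring.

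This rests on one assumption: that self-monitoring would improve cfPWV or VO2max mainly through increased activity. It does not require the instruction to have worked, because the trial has no arm from which that could be judged against uninstructed users. The size and direction of the difference cannot be derived. Sample size, randomisation and analysis model are unaffected. What changes is what the trial may conclude.

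**What to change.** **Wording.** In the abstract's Objective, the Introduction, Anticipated Findings and the planned conclusions, define the primary contrast as AI coaching that includes a goal of 2 to 3 hours of steady-state exercise a week, versus the same ring with an instruction to keep physical activity unchanged. Remove the claim that this isolates coaching beyond passive self-monitoring, and the comparison with just owning the ring. Add the control instruction to Strengths and Limitations.

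**One table.** The ring already measures leisure-time activity at baseline and during the intervention in all three arms. Report, by arm, the change from the roughly 2-week pre-randomisation period through the 12 weeks, so readers can see whether controls held their activity steady. Note beside it that this baseline is itself recorded while wearing the ring. The table therefore describes what controls did and does not replace the missing uninstructed comparator.

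**Cost.** A less favourable claim, a few sentences and one descriptive table from data already being collected. Conduct, sample size and the primary model stay as they are.
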